### Definitions

The FAS is defined as the enrolled patients excluding those who do not receive study treatment, those with serious non-compliance with ethical guidelines, and those with missing primary endpoint data. The per-protocol set is defined as patients included in the FAS, excluding those who do not meet the inclusion criteria and those with significant deviations from the study protocol. The ESD procedure time is defined as that from the beginning of the mucosal incision to the completion of tumor resection as described above. The ESD procedure time is divided into individual procedure times, namely the procedure time for the mucosal incision and submucosal dissection with or without snaring. The incision speed is defined as the circumferential length of the resected specimen/incision time (mm/min). With or without snaring, the dissection time is defined as the time from the beginning of the submucosal dissection to the completion of the tumor resection. The dissection speed, with or without snaring, is defined as the area of the resected specimen/the time of dissection, with or without snaring (mm^2^/min). The resected specimen will be flattened on the plastic plate, and the length (mm) of its long and short axes will be measured using a ruler. These measurements will be used to calculate the circumferential length (mm) and resected area (mm^2^). En bloc resection is defined as single-piece resection. Complete resection is defined as en bloc resection with free vertical and horizontal margins. Curability is divided into A, B, C-1, or C-2 based on the Japanese gastric cancer treatment guidelines [5]. Delayed bleeding is defined as clinical evidence of bleeding after the ESD procedure requiring endoscopic hemostasis or a blood transfusion. Perforation is diagnosed when mesenteric fat or intra-abdominal space is observed with a stomach wall defect during the ESD procedure or when free air is detected on X-ray or computed tomography scans after the ESD procedure is complete. When snaring is conducted for resecting the lesion, the degree of the dissected submucosal layer by the tip of the endo-knife will be assessed. The volume of the viscous solution injected using the injection needle will also be recorded. The number of hemostasis events using hemostatic forceps that occur before resection of the lesion will be counted. The time of hemostasis is defined as the cumulative time from the appearance of the hemostatic forceps on the monitor to the completion of hemostasis. Hemostasis using the endo-knife or prophylactic hemostasis for the vessels after ESD will not be recorded. The thickness of the submucosal layer in the resected specimen will be assessed just below the center of the lesion.

We will also investigate the factors associated with ESD procedure time, including tumor morphology, location, size, pathological ulceration, and operators’ experience.

Tumor characteristics will be classified according to the Japanese classification of gastric carcinoma [20]. Tumor location will be classified as the upper third, middle third, and lower third of the stomach. Tumor position will be classified as the lesser curvature, greater curvature, anterior wall, and posterior wall. Endoscopists will be classified as either expert or non-expert based on their skill with ESD. Experts are defined as endoscopists with the experience of ≥30 ESD cases for EGN. The remaining endoscopists will be defined as non-experts.

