### Endoscopic procedures

C-ESD and H-ESD procedures will be principally performed as en bloc resection. However, if en bloc resection is determined to be too difficult, preventive methods for local recurrence, such as piecemeal resection and additional coagulation using argon plasma coagulation or hot biopsy forceps, will be performed.

Both ESD procedures will be performed under sedation. C-ESD, described in detail elsewhere, consists of marking, injection, mucosal incision, and submucosal dissection [16, 17]. After observing the margin of the lesion, marking dots will be drawn 2–3 mm away from the margin. One of the viscous solutions will be injected into the submucosal layer using an injection needle to lift the target lesion. A circumferential mucosal incision will be made outside the marks. Subsequently, the submucosal layer will be dissected, and the target lesion will be retrieved. Marking, mucosal incision, and submucosal dissection will all be conducted using an endo-knife. There are no regulations for completing a circumferential mucosal incision before or during submucosal dissection in this study. The C-ESD procedure will be switched to traction-assisted ESD (TA-ESD) if the procedure time exceeds 60 min or if it is technically too difficult to ensure appropriate visualization and management of severe perforation or bleeding during C-ESD. However, TA-ESD is not considered a standard treatment because its superiority has not been shown in previous randomized controlled trials (RCTs) [18]. C-ESD can also be switched to H-ESD under the same conditions as those stated above; however, the selection of TA-ESD or H-ESD will depend on the discretion of the attending operator.

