### Outcome variables

#### Primary outcome

The primary outcome is the procedure time of each ESD among the full-analysis set (FAS). ESD procedure time is defined as the total time from the beginning of the mucosal incision to the completion of the lesion resection, including circumferential mucosal incision, submucosal dissection, snaring, and additional submucosal injections during each procedure.

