#### Secondary outcomes

The secondary outcomes are as follows: time of the mucosal incision; time and speed of the submucosal dissection, with or without snaring; en bloc and complete resection, curability, determined by histological assessment of the resected specimen; endoscopic procedural adverse events, including intraoperative perforation, delayed perforation, and delayed bleeding; degree of the dissected submucosal layer before snaring; volume of the injection solution used; number and duration of hemostasis events using a hemostatic device during the procedure; thickness of the submucosal layer in the resected specimen; and whether there was handover to another operator.

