### Study organization

The coordinating center will be established by the principal and coordinating investigators. The former will be responsible for overseeing the trial and the latter for supporting the local investigators in trial management and data recording at each participating institution. Core members of the team will meet at least once a month or more often as required during the trial period.

The steering committee will be established by the principal investigator, coordinating investigators, statisticians, and gastroenterology experts. They will monitor and evaluate the overall conduct of the trial and make recommendations regarding trial-related decisions.

An independent data and safety monitoring board will be established by experts independent from this study and its competing interests. They will monitor the trial’s progress and confirm that it has been conducted, recorded, and reported in accordance with the trial’s protocol and relevant laws, regulations, and guidelines. Both online and on-site monitoring will be used to review the trial processes. Investigators will review data on endoscopy reports, pathological results, and adverse events up to the first discharge and enter it into the INDICE cloud. They will review and manage the input data for each case.

Participants will be free to withdraw from participation at any time upon request. An investigator may terminate participation in the study if a participant meets a newly developed or not previously recognized exclusion criterion that precludes further participation, such as the occurrence of a clinical adverse event or other medical condition or situation where continuing participation would not be in the participant’s best interest. The IRB of Kyushu University may terminate the trial in the event of a safety problem.

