### Statistics

#### Hypotheses and data analysis

The primary efficacy endpoint is the procedure time of the ESD. The null hypothesis is that the procedure time for the H-ESD and C-ESD procedures in patients with EGN is the same.

Analysis of the primary and secondary outcomes will be conducted using the FAS. We plan to analyze complete cases without imputation of missing data because this trial is designed to generate little missing data.

An analysis of covariance for the logarithmically converted ESD procedure time will be conducted with tumor location (upper or middle third of the stomach vs. lower third of the stomach), tumor size (0–9 mm vs. ≥10 mm), and operators’ experience with ESD (0–29 cases vs. ≥30 cases) as covariates. H-ESD will be considered a superior treatment procedure, compared with C-ESD, if the procedure time for H-ESD is significantly shorter than that for C-ESD. A 2-sided *p*-value <0.05 will be considered to indicate statistical significance. In the sub-analysis, if a subgroup factor is one of the covariates, the analysis will be performed without including the sub-group factor as a covariate.

Statistical analyses will be performed by independent statisticians at the Data Center of the Center for Clinical and Translational Research (CCTR) at Kyushu University Hospital. The data will be transferred to SAS statistical software version 9.4 (SAS Institute INC., Cary, NC, USA) for all analyses.

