#### Sample size estimation

In this study, to test the superiority of H-ESD over C-ESD, the sample size was estimated based on the primary endpoint (the logarithmically converted procedure time for ESD). According to a previous report comparing the treatment outcomes of C-ESD and H-ESD, the logarithmically converted procedure times (minutes, mean ± standard deviation (SD)) for C-ESD and H-ESD were 1.578 ± 0.225 and 1.244 ± 0.228, respectively [12]. Considering these results, we hypothesized that H-ESD would provide a 0.2 (37%) reduction in procedure time and estimated the SD of 0.3 conservatively. Based on these assumptions, a total of 74 participants is needed to reach a power of 80% for a *t*-test with a significance level of 0.05. To compensate for a 10% dropout rate, we aim to include 82 participants in the study.

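### The full-analysis set drops patients with no procedure time, so an ESD that is begun but never completed also leaves the resection, perforation and bleeding comparisons

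*Protocol article*

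**What the plan says.** Four statements in the protocol article combine.

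- Definitions: the FAS starts from everyone enrolled and is then cut down by "excluding those who do not receive study treatment, those with serious non-compliance with ethical guidelines, and those with missing primary endpoint data". Only one other analysis set is stated, for per-protocol analysis, and it lies inside the FAS.
- Primary outcome: procedure time is "the total time from the beginning of the mucosal incision to the completion of the lesion resection".
- Hypotheses and data analysis: "Analysis of the primary and secondary outcomes will be conducted using the FAS". The same section adds: "We plan to analyze complete cases without imputation of missing data because this trial is designed to generate little missing data".
- Secondary outcomes: these include en bloc and complete resection, and "endoscopic procedural adverse events, including intraoperative perforation, delayed perforation, and delayed bleeding".

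No rule gives a value to a procedure that is started and not finished.

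**The concern.** A procedure time exists only if the resection is finished. If an ESD is started and stopped for good, the primary value is missing, the patient leaves the FAS, and the secondary outcomes go too. The perforation, bleeding or failed resection was observed, yet it is left out because a different variable is missing.

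The exclusion is decided after randomisation, by an event that the assigned technique may have caused, in an open-label trial. If such cases are more frequent in one arm, that arm's resection and complication results look better than they were. Its procedure times look shorter if the lost cases would have been slow. Accepting a complete-case analysis of time does not justify the loss from the safety and resection comparisons.

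**Working it through.** **1. The plan's own figure.** Inputs from Sample size estimation: difference 0.2 and SD 0.3 on the log10 scale, 80% power, significance level 0.05 (two-sided, from Hypotheses and data analysis). The noncentral t calculation gives 79.7% power at 36 per arm and 80.8% at 37, so 74 in total is reproduced. For dropout, 74 × 1.1 = 81.4 and 74 / 0.9 = 82.2, both consistent with 82. The effect also agrees: 1 − 10^(−0.2) = 36.9%. The sample size is not in dispute.

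**2. Who is lost.**

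| Course of the procedure | Time recorded? | In the FAS? |
|---|---|---|
| Completed as assigned | yes | yes |
| Handed over and completed (Endoscopists and equipment) | yes | yes |
| Switched technique and completed (Endoscopic procedures) | yes | yes |
| Completed piecemeal (Endoscopic procedures) | yes | yes, as an en bloc failure |
| Begun, never completed by any route | no | no |

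Only the last row is affected. The article gives no rate for it, so what follows is illustration. I take 41 per arm (82 / 2) and k uncompleted procedures, all in the H-ESD arm.

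**3. Effect on the time test with no true difference.** Both arms are drawn from a normal distribution on log10 minutes, mean 1.578 (the C-ESD mean in Sample size estimation) and SD 0.3. Then k H-ESD values are deleted and a two-sided t-test at 0.05 is run, counting significant results that favour H-ESD. The ranges are from repeated simulations of 20,000 to 100,000 trials.

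| k lost from H-ESD | Random among the slower half | Always the slowest |
|---|---|---|
| 0 | 2.5% | 2.5% |
| 1 | 3.0% to 3.1% | 4.5% to 4.7% |
| 2 | 3.6% to 3.7% | 7.0% to 7.4% |

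The spurious time reduction is about 1% (k = 1) and 2.5% to 3% (k = 2) in the middle column. In the last column the geometric mean ratio is 0.96 and 0.93, a reduction of 4% and 7%.

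**4. Effect on the estimate if the planned benefit is real.** Completers in H-ESD average 1.578 − 0.2 = 1.378. Suppose each lost case would have taken the C-ESD mean plus 2 SD, 1.578 + 0.6 = 2.178. Counting everyone, the difference is [(41 − k) × 1.378 + k × 2.178] / 41 − 1.578.

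- k = 1: 57.298 / 41 − 1.578 = −0.180, a 34% reduction.
- k = 2: 58.098 / 41 − 1.578 = −0.161, a 31% reduction.

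The FAS would show 37% in both cases.

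**5. Effect on safety and resection.** If each lost case carries an event and completers have none, the FAS shows 0 / (41 − k) where the true rate is k / 41. That is 0/40 against 1/41 (2.4%), or 0/39 against 2/41 (4.9%). Uncompleted resections hide failures of en bloc and complete resection in the same way.

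**6. Power.** Under the planned effect, power is 84.7% with 41 and 41 patients and 83.7% with 39 and 41. The issue is selection, not power.

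**The case against.** The strongest reply is that the protocol is built so that procedures get finished. Long procedures, heavy bleeding and perforation are grounds for handover. A difficult C-ESD can be switched to a traction-assisted or hybrid procedure, and a difficult H-ESD to C-ESD. Where en bloc resection is too hard, "preventive methods for local recurrence, such as piecemeal resection and additional coagulation using argon plasma coagulation or hot biopsy forceps, will be performed". Lesions are at most 20 mm and not ulcerated. This stands: a reader might infer that every complicated procedure drops out, and the documents do not support that.

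Three further inferences are tempting and also fail.

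- The dropout allowance, "To compensate for a 10% dropout rate, we aim to include 82 participants in the study", could be read as the expected number of uncompleted procedures, about four per arm. The article does not say so. The allowance may equally cover patients who withdraw or are never treated. At four lost H-ESD cases the false-positive rate would be about 14.5% (always the slowest) or 5.4% (slower half), but no document supports that count. Nor does the allowance contradict an expectation of little missing data among treated patients.
- Study organization says "An investigator may terminate participation in the study if a participant meets a newly developed or not previously recognized exclusion criterion", and gives adverse events as an example. It does not say that data already collected are discarded, and a recorded time is not lost through a later event.
- Safety information does not vanish. Adverse events are recorded and entered up to first discharge, serious ones are reported, and the planned CONSORT report would show exclusions. What is lost is the patient's place in the between-arm comparison.

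The simulation is also one-sided, with all losses in H-ESD. With the two slowest lost from H-ESD and the slowest one from C-ESD, the rate is about 5%. There is no bias if no procedure is left uncompleted or if loss is unrelated to time, and losses concentrated in C-ESD would push the other way. None of this defends removing an observed complication from its own comparison.

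**Conclusion.** The point holds in a limited form. The stated definitions remove a begun but uncompleted ESD from the time analysis and from the resection and complication comparisons, and no other stated analysis set restores it. For the safety and resection outcomes the defect follows from the wording whenever one such case occurs, at up to 2.4 percentage points per case in an arm of 41. For the time test, one or two losses confined to H-ESD move the false-positive rate from 2.5% to about 3% to 4%, or about 5% to 7% at worst. These sizes rest on assumed numbers and an assumed pattern of loss. The real number is probably small, and the bias in time could run in either direction. Severity: should-fix.

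**What to change.** - **Definitions:** delete the third exclusion in "excluding those who do not receive study treatment, those with serious non-compliance with ethical guidelines, and those with missing primary endpoint data". Subject to the ethics exclusion, the FAS then keeps all randomised patients in whom ESD was begun, in the arm to which they were allocated.
- **Hypotheses and data analysis:** analyse resection outcomes and adverse events in all of these patients, counting an uncompleted resection as a failure of en bloc and of complete resection.
- **Primary analysis:** keep the planned ANCOVA on recorded times. Record the stop time of any uncompleted procedure and report the number by arm. Add a sensitivity analysis that gives such cases an unfavourable time, for example a worst-rank comparison.

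I would not replace the ANCOVA with a censored log-normal regression. Stopping for a complication is informative censoring, which that model assumes away. Its default maximum-likelihood Wald test also divides the variance by n and uses a normal reference. With five parameters this puts the nominal 5% level at about 6.1% (n = 82) or 6.3% (n = 74), even with nothing censored.

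The cost is a change of wording in two sections, one stop time per uncompleted case and a little more analysis. No extra patients are needed. Safety and resection results may look slightly less favourable.

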### Endoscopists and equipment

Each procedure will be performed at one of the nine institutions by one of the participating endoscopists; each endoscopist in this study has been licensed to practice medicine in Japan for at least 2 years and has performed ≥500 endoscopies. Endoscopists without experience in C-ESD or H-ESD will be required to undergo hands-on training using a pig model before becoming an operator in the study. Handover of the procedure to another operator will be allowed if experienced endoscopists consider the handover clinically desirable for reasons such as prolonged procedure time over 60 min, massive uncontrollable bleeding, or the occurrence of perforation during the procedure. Procedure handover will be done and recorded if the supervisor determines that it is necessary.

Upper gastrointestinal endoscopes (EG-450-RD5, Fujifilm, Tokyo, Japan; GIF-Q260J, Olympus, Tokyo, Japan) attached to a disposable hood (Elastic touch, Top, Tokyo Japan, or D-201-11804, Olympus) will be used in the ESD procedures. A Flush Knife (DK2620J, Fujifilm) or Dual Knife (KD-650, Olympus) will be used in the C-ESD procedure. A SOUTEN (ST1850-20, Kaneka Medix, Tokyo, Japan) will be used in the H-ESD procedure. The SOUTEN is a hybrid knife that combines a needle knife and a snare, where a needle tip is attached to the top of the snare. No regulation is required for the types of injection needles in this study. An electrosurgical unit (ICC200, VIO300, or VIO3, ERBE, Tubingen, Germany) will be used as a high-frequency generator. Sodium hyaluronate solution or sodium alginate solution will be used as a viscous solution for submucosal injections from the injection needle. Normal saline or glycerol will be used for submucosal injections using the endo-knives. Coagrasper (FD-410LR, Olympus), Coagrasper G (FD-412LR, Olympus), RAICHO (RC-1900, Kaneka Medix), RAICHO 2 (RC1550-2, Kaneka Medix), and Hemostat Y (H-S2518, Pentax, Japan) forceps will be used if bleeding cannot be controlled using the endo-knife.

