The H-ESD procedure will be performed, as described in detail elsewhere, using a SOUTEN high-frequency surgical knife [12, 19]. SOUTEN will be fixed with the snare closed, and only the distal tip will be exposed. Marking, injection, and mucosal incision will be performed in the same manner as described for C-ESD using the tip of the SOUTEN and an injection needle. After completing the circumferential incision, a partial submucosal dissection will be performed using the tip of the SOUTEN. Snaring of the lesion will be performed once the operator considers it possible to perform the resection in an en bloc manner. The open snare will be placed around the lesion, which will subsequently be resected by closing the snare and coagulation. H-ESD can also be switched to C-ESD if the operator considers snaring too difficult to perform. In such cases, the submucosal dissection will be performed until the specimen is retrieved.

Injection of the viscous material can be performed in both C-ESD and H-ESD using an injection needle, but it can also be done in C-ESD using an endo-knife. Hemostasis will be performed in both C-ESD and H-ESD using the tip of the devices if bleeding occurs or if the blood vessels are detected. If bleeding cannot be controlled using only an endo-knife, hemostatic forceps will be used.

Patients will be managed as after regular ESD, including being managed with intravenous nutrition and fasting. Patients will start to receive proton pump inhibitors, including potassium competitive acid blockers after ESD. Enteral diets will start within 2 or 3 days after ESD. If there are no serious adverse events (AEs), patients will be discharged approximately 1 week after ESD. If any AEs occur, investigators will immediately provide appropriate treatment and record it. The endoscopic treatment performed in this study is covered by the current medical insurance, and all costs associated with the study, including the treatment of AEs, will be charged and paid in accordance with the medical insurance system. There is no special compensation system for side effects caused by these treatments.

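### Dissection time, dissection speed and injection volume are defined so that they can measure different things in the two arms wherever C-ESD operators overlap incision with dissection or inject through the knife

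*Protocol article*

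**What the plan says.** **Phase times.** The Definitions section divides procedure time into mucosal incision and submucosal dissection, with or without snaring. It then says that "the dissection time is defined as the time from the beginning of the submucosal dissection to the completion of the tumor resection". Dissection speed "is defined as the area of the resected specimen/the time of dissection, with or without snaring". Incision speed is the specimen's circumferential length over incision time, but the start and end of incision time are not defined.

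**Order of the phases.** Under Endoscopic procedures, the C-ESD description says: "There are no regulations for completing a circumferential mucosal incision before or during submucosal dissection in this study". The H-ESD description fixes the order: "After completing the circumferential incision, a partial submucosal dissection will be performed using the tip of the SOUTEN".

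**Injection volume.** The Secondary outcomes section lists the "volume of the injection solution used". The Definitions section gives the measure: "The volume of the viscous solution injected using the injection needle will also be recorded".

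**Route and solution.** Endoscopists and equipment assigns viscous solution to the injection needle and adds: "Normal saline or glycerol will be used for submucosal injections using the endo-knives". Endoscopic procedures speaks of injecting viscous material by needle in both arms, "but it can also be done in C-ESD using an endo-knife". The Discussion says that the H-ESD device performs every step except submucosal injection.

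**The concern.** A dissection clock that starts at the first dissection and stops at resection isolates dissection only if the incision is already complete. The procedure as described guarantees this in H-ESD and not in C-ESD, so one definition can measure pure dissection in one arm and a mixture in the other. The volume measure has a similar gap: the route it leaves out is described for one arm only.

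The two effects run in different directions. The timing effect makes C-ESD dissection look slower, which is the direction of the trial's hypothesis. The volume effect makes C-ESD appear to use less solution, so H-ESD could seem to need more. All of these are listed secondary outcomes to be compared between arms. If the overlap and the knife volume are not captured during the procedure, no later analysis can recover them.

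**Working it through.** The plan gives no figure for this point: no incision share, no extent of overlap and no knife volume. The check is therefore algebra on the definitions, followed by an illustration on stated assumptions.

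**1. Dissection time and speed.** Let I be the true time spent on mucosal incision, D the rest of the procedure, T = I + D the total, A the specimen area, and f the fraction of the incision done after dissection starts.

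- H-ESD as described: f = 0.
- C-ESD as described: f may be anything from 0 upward.
- Recorded dissection time = D + fI. With r = I/D, recorded/true = 1 + fr.
- Recorded speed = A/(D + fI), so recorded/true = 1/(1 + fr).

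**2. Incision time, under the two available readings.**

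- It ends when dissection starts: recorded incision time = (1 − f)I. The parts sum to (1 − f)I + D + fI = T. Incision time is then understated in C-ESD, and incision speed is overstated by 1/(1 − f).
- It is all time spent incising: recorded incision time = I. The parts sum to I + D + fI = T + fI, which exceeds the total.

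Dissection time is overstated by fI under both.

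**3. Illustration (r and f are assumptions).**

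| r | f | Recorded/true dissection time | Recorded/true speed | Shift on log10 scale |
|---|---|---|---|---|
| any | 0 | 1.00 | 1.00 | 0 |
| 0.25 | 0.10 | 1.025 | 0.976 | 0.011 |
| 0.50 | 0.25 | 1.125 | 0.889 | 0.051 |
| 1.00 | 0.50 | 1.50 | 0.667 | 0.176 |

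For scale only, the planned effect on total procedure time is 0.2 on the log10 scale (10^−0.2 = 0.63, the plan's 37% reduction).

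In minutes, the sample size section's C-ESD log mean of 1.578 back-transforms to 10^1.578 = 37.8. With r = 0.5, I = 12.6 and D = 25.2. With f = 0.25, recorded dissection time is 25.2 + 0.25 × 12.6 = 28.35 min, and 28.35/25.2 = 1.125.

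Under the first reading in step 2, f = 0.10 to 0.50 would overstate C-ESD incision speed by a factor of 1/0.9 = 1.11 to 1/0.5 = 2.0.

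**4. Injection volume.** Let q be the share of C-ESD solution given through the knife. The recorded C-ESD volume is (1 − q) of the total. H-ESD as described has q = 0. Equal true totals would then appear as an H-ESD/C-ESD ratio of 1/(1 − q):

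- q = 0: 1.00
- q = 0.10: 1.11
- q = 0.25: 1.33
- q = 0.50: 2.00

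These values of q are also assumptions.

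**5. What the volume measure means depends on which section governs.**

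- If the knife carries only saline or glycerol (Endoscopists and equipment), needle-given viscous volume is complete as a viscous volume, but it is not the solution used.
- If viscous material can also go through the knife in C-ESD (Endoscopic procedures), even the viscous volume is incomplete in that arm.

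**6. Primary outcome.** Total procedure time runs from the start of the mucosal incision to completed resection in both arms. Neither I, D nor f is needed to measure it.

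**The case against.** The strongest reply has four parts.

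- **Incision time is not defined.** If it is read as ending when dissection starts, the two parts add up in both arms. This is right, and a reader should not infer that the parts cannot sum to the total. It does not rescue the comparison: dissection time still contains incision work, and the error reappears as a C-ESD incision time that is too short.
- **The text does not say that other volumes go unrecorded.** It says that needle-given viscous volume is also recorded, whereas it expressly excludes endo-knife hemostasis from recording. Knife volume may therefore be captured elsewhere. That is possible, but the only measure the article defines for this outcome leaves it out. If the equipment section governs, the remaining defect is a mismatch between the outcome's name and its definition.
- **Use of these freedoms is not known.** A reader might infer that the comparisons are certainly biased and that only C-ESD is mismeasured. The documents do not support either. Overlap and knife injection are permitted, not required. H-ESD may be switched to C-ESD, and a switched patient analysed in the H-ESD arm could also be affected, for example by knife injection.
- **The primary outcome and sample size are untouched, and no passage assigns these secondary outcomes an explanatory role.** Both statements are correct and limit the weight of the point.

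What stands is that stated rules, followed as written, can measure listed outcomes differently by arm. That goes beyond detail an article would leave to the full protocol.

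**Conclusion.** The point holds in a conditional form. Where C-ESD operators complete the incision during dissection, C-ESD dissection time is overstated and dissection speed understated. If incision time is taken to end when dissection starts, C-ESD incision time is also understated and incision speed overstated. Where they inject through the knife, that solution is not counted in the volume measure.

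The size of either bias cannot be computed from the documents and may be zero. The illustrative ranges (dissection time 1.03 to 1.50 times true, apparent volume ratio 1.11 to 2.0) rest wholly on assumed shares and should not be quoted as estimates. The superiority test is not at risk. The point concerns the interpretation of secondary outcomes and is worth correcting, because the missing information cannot be reconstructed in the analysis.

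**What to change.** In the Definitions section:

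1. Define incision time as the cumulative time spent on mucosal incision, and dissection time as total procedure time minus incision time, by the same rule in both arms. Compute both speeds from these. The parts then sum to the total by construction.
2. Record injected volume by every route and by solution, and compare totals. Alternatively, rename the outcome as needle-injected viscous volume and do not interpret it as total volume.
3. Reconcile Endoscopists and equipment with Endoscopic procedures on which solution is given through the knife.

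The cost is revised wording and a few more case-report-form entries. The one practical burden is that incision segments must be timed separately when the phases are interleaved. The plan already times hemostasis cumulatively, so this kind of recording is not new to the trial. No change to either procedure is needed.
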